# **Statistical analytical plan**

Mixed models repeated measures (MMRM) analyses, with maximum likelihood estimation and an appropriate covariance structure, will be used to evaluate longitudinal changes in suicidal ideation and secondary mental health outcomes between the LifeBuoy and attentional control arms. Where required, generalised linear mixed models with an appropriate link function will be used for the analysis of categorial variables. The primary outcome is severity of suicidal ideation, as measured by the Suicidal Ideation Attributes Scale [SIDAS], over time (baseline T0, 30-days T1, 60-days T2, and 120-days T3). The mixed model approach incorporates all available data, including participants with missing follow-up data points, under the missing-at-random assumption. Analyses will therefore accord with the intention-to-treat principle.

Descriptive statistics will be used to examine the level of engagement in three arms (LifeBuoy, LifeBuoy + engagement, and control). Engagement will be measured by the number of modules completed by participants. Participant module access and module completion will be automatically collected via the app.

Qualitative feedback on users’ perceived acceptability of the LifeBuoy app and engagement strategy will be examined through semi-structured interviews with a subset of participants (n=30 in total) and questionnaires in the survey. The interview data will be analysed using thematic analysis. An inductive approach, independent of a theoretical confirmative method will be used to identify and group themes. The researchers will then refine the themes and determine the final coding framework. Discrepancies will be resolved by a third researcher to ensure reliability of the process.

Any deviation from the original statistical plan will be described and justified in the final report.

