**Safety Analyses**

Suicidal behaviour (ideation, attempts, and NSSI)

- Suicidal ideation, as measured by % scoring >20 on the SIDAS
- A suicide attempt during the trial identified at all follow up surveys: “Since the last LifeBuoy study survey, how many times have you made an attempt to kill yourself in which you had some intent to die?” >0 (T1 – T3) or ad hoc self-report by participants to research study email.
- Non-suicidal self-injury during the trial identified at all follow up surveys: “Since the last LifeBuoy study survey, how many times have you injured yourself on purpose without suicidal intent (i.e., intentional, self-inflicted damage to the surface of the body but with no intent to die)?” >0 (T1 – T3) or ad hoc self-report by participants to research study email.
- Serious adverse events (including all events requiring medical intervention).
- Enrolment data, intervention completion data, attrition data, adverse event data, and other administrative data.

The TSG cannot access the unblinded data for suicidal ideation, attempt, or NSSI as these are outcome measures and will be shared only in a closed session.

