| (If 2 or 3) How many sessions have you had with your current mental health professional? | (free numerical response) | 0 to 1000 |
| What is the longest you have stayed with a mental health professional | --- select ---- | N/A  Less than a month (1)  1 to 3 months (2)  3 to 6 months (3)  6 to 12 months (4)  1 to 2 years (5)  More than 2 years (6) |

Now we’re going to ask you some questions about suicidal thoughts, and the severity of them. Please think about the past 30-days when answering the following questions.

[Suicidal Ideation Attributes Scale] (SIDAS)

| Question | Response options |
| --- | --- |
| In the past month, how often have you had thoughts about suicide? | 0 (Never), 1,2,3,4,5,6,7,8,9, 10 (Always) |
| In the past month, how much control have you had over these thoughts? | 10 (Full control), 9, 8, 7, 6, 5, 4, 3, 2, 1, 0 (No control) |
| In the past month, how close have you come to making a suicide attempt? | 0 (Not close at all), 1,2,3,4,5,6,7,8,9, 10 (Made an attempt) |
| In the past month, to what extent have you felt tormented by thoughts about suicide? | 0 (Not at all), 1,2,3,4,5,6,7,8,9, 10 (Extremely) |
| In the past month, how much have thoughts about suicide interfered with your ability to carry out daily activities, such as work, household tasks or social activities? | 0 (Not at all), 1,2,3,4,5,6,7,8,9, 10 (Extremely) |
| **Note:**Respondents who respond “0 – Never” to the first item skip all remaining items and score a total of zero. **Note:** item 2 is reverse scored.  **Scoring:** add total (range from 0 to 50) | |

We’d just like to ask you a few questions about prior self-harm thoughts and behaviours. Please look after yourself as you go through these questions and take breaks as needed.

[Other suicide-related questions] (Other_SI)

| What the user will see | | Drop down response options available |
| --- | --- | --- |
| How many times have you made an attempt to kill yourself in which you had some intent to die?  *Baseline only* | (free numerical response) | Participant to type in the number |
| (If >0) How many suicide attempts were made in the past 12 months?  *Baseline only* | (free numerical response) | Participant to type in the number |
| (If >0) How many suicide attempts were made in the past 30 days? | (free numerical response) | Participant to type in the number |

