| (If yes to the past 30 days)  In the most severe suicide attempt in the past 30 days: | - Select all that apply - | No care was needed (0)  I attended the hospital, but without physical injury and left without being admitted (1)  I attended the hospital with a physical injury but left without being admitted (2)  I was admitted to hospital without physical injury (3)  I was admitted to hospital with physical injury (4) |
| How long have you been experiencing suicidal thoughts?  *Baseline only* | --- select ---- | 3 months or less (1)  Up to 12 months (2)  More than 12 months (3)  More than two years (4)  More than five years (5) |
| At what age did you first experience suicidal thoughts?  *Baseline only* | (free numerical response) | Participant to type in the number |
| Have you ever injured yourself on purpose *without suicidal intent* (i.e., intentional, self-inflicted damage to the surface of the body *with no intent to die*)  *Baseline only* | --- select ---- | No (0)  Yes (1) |
| (If yes) How many times have you injured yourself on purpose in the past 12 months?  *Baseline only* | (free numerical response) | Participant to type in the number |
| (If >0) How many times have you injured yourself on purpose in the past 30 days? | (free numerical response) | Participant to type in the number |
| (If past 30 days more than 0) In the most severe self-injury over the past 30-days (please select one): | --- select ---- | No medical care was needed (0),  I treated the injury myself (1),  I attended a medical clinic or hospital and left without being admitted (2),  I was admitted to hospital (3) |

[Patient Health Questionnaire-9] (PHQ-9)

| Over the last **2 weeks**, how often have you been bothered by the following problems? | Not at all | Several days | More than half the days | Nearly every day |
| --- | --- | --- | --- | --- |
| Little interest or pleasure in doing things | 0 | 1 | 2 | 3 |
| Feeling down, depressed, irritable, or hopeless | 0 | 1 | 2 | 3 |
| Trouble falling asleep, staying asleep, or sleeping too much | 0 | 1 | 2 | 3 |
| Feeling tired, or having little energy | 0 | 1 | 2 | 3 |
| Poor appetite, weight loss, or overeating | 0 | 1 | 2 | 3 |
| Feeling bad about yourself — or feeling that you are a failure, or that you have let yourself or your family down | 0 | 1 | 2 | 3 |
| Trouble concentrating on things, such as reading the newspaper or watching television | 0 | 1 | 2 | 3 |

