**Flagging procedure**

**1)** At each survey timepoint (baseline, 30-days, 60-days, and 120-days) three items indicates risk of suicide. When a selection is made indicating a concerning level of suicidal thinking (SIDAS score >20), a suicide attempt during the trial, or NSSI requiring medical care during the trial, an automated alert system is triggered, where an automated email is sent to the participant asking if they would like to receive a phone call from the team clinical psychologist during business hours (9:00 to 17:00 AEST) within the next 3 working days. This email will also include a list of crisis contact numbers for support.

*“Hi there,*

*Thanks so much for signing up to participate in the study and for completing the latest survey. We noticed that your responses on the survey indicate a recent self-harm event or severe current suicidal thoughts. If you would like to receive a phone call from our clinical psychologist during business hours (9:00 to 17:00 AEST) within the next 3 working days, please click ‘reply’ to this email or send a new email request to [contact]*

*If you’ve had a tough time with your mental health lately, we encourage you to talk to a local doctor or mental health professional about how you’re feeling. If you would like to know where to get some immediate help, here are some suggestions:*

- *Lifeline: [name]*
- *Kids Helpline :[name]*
- *Suicide Callback Service: [name]*

*For 24-hour advice on what to do and who to contact, don’t hesitate to visit HealthDirect (https://www.healthdirect.gov.au) or call them at [name]).*

*If you feel in danger or that you might hurt yourself, do not hesitate to call Emergency Services on 000.*

*Warm regards*

*The LifeBuoy team”*

(*Note:* at the completion of each survey all participants will be shown a screen with the same abovementioned support contacts).

**2)** If a flagged participant indicates they would like a call back, the team clinical psychologist ([name]) will contact the participant via phone as soon as possible. This discussion will centre around making sure the young person is supported in their family and/or community and identifying how they can access the services they need. If the participant expresses distress in relation to using the app or answering the assessment questionnaires, they will be reminded of their right to withdraw from the trial without penalty or the need for explanation.

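### An attempt reported on SIDAS item 3 can stand as no attempt, because attempts are identified from a separate question whose window and display condition are stated inconsistently

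*Protocol*

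**What the plan says.** **SIDAS.** Under Outcome measurement surveys, item 3 asks how close the participant came to an attempt in the past month, answered on "0 (Not close at all), 1,2,3,4,5,6,7,8,9, 10 (Made an attempt". Those who answer never "to the first item skip all remaining items and score a total of zero", so item 3 is seen only when item 1 is above 0. Scoring is "add total (range from 0 to 50". SIDAS is the primary outcome, measured "over time (baseline T0, 30-days T1, 60-days T2, and 120-days T3".

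**Attempts, charter version.** The Safety Analyses section lists "A suicide attempt during the trial identified at all follow up surveys", using a question about the period since the last survey: "how many times have you made an attempt to kill yourself in which you had some intent to die". An attempt is a count above zero at T1 to T3, or an unprompted report to the study email. SIDAS appears in that list only as the percentage above 20.

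**Attempts, survey version.** The survey tables print a lifetime count and a 12-month count, both marked as baseline only. A past-30-days count follows, shown if the answer is above zero. The care-received question, "In the most severe suicide attempt in the past 30 days", opens only on a positive 30-day count.

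**Uses of the attempt report.** Attempts are in the first secondary objective (Trial Objectives and Purpose). The Serious Adverse Event definition and the relatedness question under Serious Adverse Reaction refer to participants who report an attempt. The Flagging procedure says "three items indicates risk of suicide" and names a SIDAS score above 20, an attempt, and self-injury needing medical care. None of these sections says which survey item counts as reporting an attempt.

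**The concern.** The same questionnaire offers two places to report an attempt, and only one is tied to the attempt definition and to the care-received question. Where the two disagree, or only SIDAS item 3 is answered, the record can show the maximum item score in the primary scale and no attempt in the safety table.

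What is at stake is the data collected, not only a derivation. If the care-received question was never displayed, no later programming can establish whether care was needed, and that bears on whether the event meets the Serious Adverse Event definition. Attempts are also a secondary outcome and a DSMB safety measure.

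**Working it through.** **1. The plan's own figure.** Five items scored 0 to 10, with item 2 reversed and a total of 0 if item 1 is 0, give a range of 0 to 50. This matches the stated range.

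**2. Does the SIDAS flag (total above 20) catch every item 3 = 10 answer?** Set item 3 to 10. Item 1 must be 1 to 10 and the other three scored items run from 0 to 10.
- Patterns: 10 × 11³ = 13,310.
- Minimum total: 1 + 0 + 10 + 0 + 0 = 11.
- Total of 20 or less requires the four remaining items to sum to 10 or less with item 1 at least 1. The number of such patterns is C(13,4) = 715, confirmed by full enumeration.
- 715 / 13,310 = 5.4% of patterns.
- Example: item 1 = 2, item 2 at full control (scored 0), item 3 = 10, item 4 = 3, item 5 = 2, total 17, which is not flagged on the SIDAS score.

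The 5.4% weights every pattern equally and says nothing about how often such answers occur. When the flag does fire, it sends an email; the procedure does not say that it records an attempt.

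**3. Recall windows.**

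| Survey | Days since last survey | Charter question covers | Survey 30-day item covers | Missed by 30-day item |
| --- | --- | --- | --- | --- |
| T1 | 30 | 30 | 30 | 0 |
| T2 | 60 − 30 = 30 | 30 | 30 | 0 |
| T3 | 120 − 60 = 60 | 60 | 30 | 30 |

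SIDAS item 3 also looks back one month, so it cannot recover the 30 days missed before T3. Only settling the window can.

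**4. Routes by which item 3 = 10 stands as no attempt.**
- *Count answered 0:* the participant contradicts the item 3 answer, or uses 10 without meaning an attempt.
- *Count skipped:* the charter's rule needs a count above zero, so a blank does not qualify.
- *Count not shown:* the 30-day item is conditional on a preceding answer, and the preceding items are baseline only. If the condition reads the baseline answer, someone who reported no attempt at baseline is not asked at T1 to T3. A first attempt after baseline would then appear, among the survey items, only in SIDAS item 3, even for a fully consistent respondent. The charter wording implies that the question is put at all follow-ups. The protocol does not settle which version is fielded.

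In each case the care-received question stays closed, because it is conditional on the 30-day count.

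**5. Number affected.** The protocol gives no attempt rate and no rate of disagreement between the two items, so this cannot be calculated.

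**The case against.** The strongest reply is that a dedicated item is the better definition. The charter question is an explicit count, requires some intent to die, and covers the whole interval since the last survey. Item 3 is a closeness rating that does not define an attempt, and some people may choose 10 to mean extremely close. Some disagreement between the items is therefore legitimate. Moreover, a consistent respondent who is shown the charter question is counted, and a rule for reconciling two self-reports is commonly left to the SAP. All of this stands. It is why item 3 = 10 should not replace the dedicated definition. It does not answer the display conditions, which this document fixes and an SAP cannot repair after data collection.

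Three stronger readings are tempting and are not supported:
- **That such participants certainly receive no serious adverse event assessment or relatedness question.** The Serious Adverse Event, Serious Adverse Reaction and Flagging procedure sections name no source item and could be read to include item 3. Only the care-received question is clearly tied to the count.
- **That a definite number of attempts is lost.** Assuming that 2–8% of 669 report an attempt and 10–30% of them answer discordantly gives 669 × 0.02 × 0.10 = 1.3 to 669 × 0.08 × 0.30 = 16.1. Neither rate is in the protocol, and the base ignores the 25% attrition assumed under Sample Size.
- **That the primary outcome or the comparison between arms is biased.** The SIDAS total is scored as specified, and nothing shows that discordance would differ by arm. The charter's list is also a safety definition; the protocol fixes no derivation of attempts for the efficacy analysis.

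**Conclusion.** The point holds as a gap in safety capture combined with an internal inconsistency. An item 3 answer stating that an attempt was made can coexist with a record of no attempt and an unasked care-received question. If the charter question is put to everyone at T1 to T3, this needs a discordant or missing answer. If the survey is fielded as printed and the condition reads baseline answers, it can happen to consistent respondents, and the 30-day item also leaves 30 of the 60 days before T3 uncovered.

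The SIDAS flag is an incomplete back-up, since totals of 11 to 20 are possible with item 3 at 10. The size in participants is unknown. No sample size, power or primary-outcome figure changes. The change is worth making because it is cheap and the unasked answers cannot be recovered later.

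**What to change.** 1. Reconcile the charter's Safety Analyses with the survey tables on recall window and display condition, so that one version of the count question is put to every participant at T1, T2 and T3. Align the window of the care-received question with it.
2. Let item 3 = 10 at T1 to T3 act as a second condition that opens the existing care-received question and, on the terms already set, the relatedness question.
3. Keep the dedicated question as the main attempt definition. Report by arm, as a sensitivity count, attempts by either source, with the number discordant.
4. Reconcile the Serious Adverse Event, Serious Adverse Reaction and Flagging procedure sections on which item counts as a reported attempt.

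The cost is a change to survey display rules, one derivation line and some aligned wording; no new item is needed. The downside is that some respondents may use 10 to mean extremely close, so the either-source count may include non-attempts. That is why it sits beside the dedicated count and does not replace it.

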In this trial a Serious Adverse Event (SAE) is o one or more of the following events and the event is not related to the trial intervention:

1. A participant reporting a suicide attempt or NSSI that requires medical care at any follow-up assessment time point.
2. If we become aware of a death of a participant during the trial, for any reason, this will also be considered a serious adverse event.

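### The survey item on care after a suicide attempt has no answer for non-hospital care or unmet need, and unreconciled SAE wording leaves open whether such attempts can miss SAE classification

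*Protocol*

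**What the plan says.** All places are in the Protocol or the DSMB Charter within it.

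- **Outcome measurement surveys, Other suicide-related questions (attempt item).** A participant with an attempt in the last 30 days is asked about care after the worst one. The list runs from "No care was needed (0) I attended the hospital, but without physical injury and left without being admitted (1" to "I was admitted to hospital with physical injury (4". More than one answer may be ticked.
- **Same section (NSSI item).** One answer only. The options include treating the injury oneself and "I attended a medical clinic or hospital and left without being admitted (2".
- **Types of Safety and Monitoring, Serious Adverse Events.** The first SAE criterion is "A participant reporting a suicide attempt or NSSI that requires medical care at any follow-up assessment time point". The Serious Adverse Reaction section uses the same construction to decide who is asked whether the study or app contributed to the event.
- **Risk Management Protocol, Flagging procedure.** Besides a high SIDAS score, the alert is triggered by "a suicide attempt during the trial, or NSSI requiring medical care during the trial". The charter's Trial Stopping Guidelines define at-risk participants in the same form.
- **DSMB Charter, Safety Analyses.** Attempts and NSSI are counted from every follow-up survey "or ad hoc self-report by participants to research study email".

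**The concern.** The graver event has the less complete question. A participant whose attempt was treated outside hospital, or who needed treatment and did not get it, cannot answer truthfully. Code 0 is the only answer that does not claim a hospital visit. This is also the only item shown that records care after an attempt, so if the SAE definition depends on care, nothing else shown in the survey supplies the fact.

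Two things are at stake. One is the SAE label, which has its own reporting route to the DSMB. The other is the relatedness question, which is the Protocol's stated means of judging whether the trial contributed. The charter's Reporting section expedites an SAE only if it is both unexpected and possibly related, so an attempt that never reaches that question loses the participant's answer on relatedness.

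A second, separate mismatch concerns the reporting route. The SAE definition and the relatedness trigger are tied to follow-up assessments, while the charter's safety count also accepts email reports. A participant who emails about an attempt and then misses the survey is in the count but outside the wording of the SAE definition.

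**Working it through.** No sample-size or event calculation applies. The check sets the passages side by side.

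**Step 1: coverage of the options.**
- Attempt item: 5 options. One says no care was needed and 4 are hospital answers (1 + 4 = 5). That leaves 0 of 5 for a clinic, GP or ambulance, self-treatment, or unmet need.
- NSSI item: 4 options. One says no medical care was needed, one is self-treatment, one is a clinic or hospital without admission, and one is admission. It also lacks an unmet-need answer, but it does cover care outside hospital.
- Multiple ticks on the attempt item allow contradictory answers about one event, such as admitted and not admitted. Any of codes 1 to 4 still shows hospital attendance, so this is a data-quality fault and not a route by which an SAE is lost.

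**Step 2: what follows under each reading of the SAE definition.** Reading A applies the care condition to attempts and NSSI. Reading B applies it to NSSI only, as in the Flagging procedure and the Trial Stopping Guidelines.

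| Attempt reported in a survey | Answer available | Reading A | Reading B |
|---|---|---|---|
| Truly needed no care | Code 0, correct | Not an SAE, correctly | SAE |
| Hospital attended or admitted | Codes 1–4, correct | SAE | SAE |
| Care from a clinic, GP or ambulance only | None true; code 0, a blank or a false hospital code | SAE by definition, but can be missed | SAE |
| Needed care, got none | None true; same choices | SAE by definition, but can be missed | SAE |

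The loss is confined to the last two rows under reading A. A blank is no remedy there, because it does not establish that care was required.

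**Step 3: what is captured regardless.** Under both readings a survey-reported attempt triggers the alert. It also enters the DSMB's attempt count, which takes any number above zero whatever care was received.

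**Step 4: the reporting route.** SAE definition and relatedness trigger: follow-up assessments only. Charter Safety Analyses: follow-up surveys plus email. The two do not match under either reading.

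**Step 5: size.** The Protocol gives no attempt rate and no breakdown of where care is received. Two of its figures may look usable but are not:
- The Background's under-30% help-seeking figure concerns mental health services among people with ideation, plans or attempts. It does not describe medical care after an attempt.
- The 25% attrition assumed at 30 days gives 0.25 × 669 ≈ 167 participants without a T1 survey. It does not say how many of them would attempt suicide or email the team.

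**The case against.** The strongest reply has four parts.

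1. **No text makes this item the decision rule.** The response codes are nowhere mapped to SAE status. Types of Safety and Monitoring gives classification to a safety flow chart, with SAE reports assessed by the sponsor's independent medical assessor. The flow chart is not shown and may hold the mapping. The survey pages may also be incomplete: neither the follow-up attempt question quoted in the charter nor the relatedness question appears in them. This stands. The item can be called only the one attempt-care item shown.
2. **Two sections support reading B.** If the SAE definition means the same as they do, no answer can remove an attempt from the SAE count. This also stands, and it makes the SAE consequence conditional. It does not remove the need to settle the wording, since the definition and the relatedness trigger both use the other form.
3. **The DSMB sees these events anyway.** The charter counts every attempt, including those reported by email, and makes attempt data available in closed session. It also requires the investigators to monitor the inbox and report safety concerns promptly, and tells the steering group to report when in doubt. This largely stands. It does not restore the SAE label or the relatedness question.
4. **Code 0 is not always wrong.** An untreated attempt that needed no treatment is correctly coded. Only non-hospital care and unmet need are misrecorded, and since no forced response is stated, the item might be left blank. This stands.

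A reader might infer that SAE counts by arm will be understated, or that the DSMB will be blind to these attempts. The documents do not support either. The first needs reading A and an unknown number of such events; the second is contradicted by the charter's attempt count.

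**Conclusion.** The point holds in a limited form. The attempt item's options are not exhaustive and do not match those of the NSSI item beside it, so the care recorded for some attempts would be wrong or absent if the survey were run as written. That part needs no assumption about the SAE definition.

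The SAE consequence rests on two assumptions: that the care condition covers attempts, and that this item informs the assessor's classification. If both hold, an attempt treated outside hospital, or with unmet need, can miss the SAE label and the relatedness question. If the condition covers NSSI only, no attempt is lost. The size cannot be estimated from the documents, and any percentage would be a guess.

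The mismatch over email reports is a separate inconsistency that holds on either reading. Its effect too is limited to SAE status and the relatedness question, because the charter already counts those reports.

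**What to change.** 1. **Attempt item (Outcome measurement surveys).** Add answers for care outside hospital, self-treatment, and care needed but not received. Make it single-choice like the NSSI item. Adding the unmet-need answer to the NSSI item as well would keep the two aligned.
2. **SAE definition and relatedness trigger (Types of Safety and Monitoring).** Reconcile both with the Flagging procedure and the Trial Stopping Guidelines on whether the care condition applies to attempts. State which response codes meet it, or refer to the flow chart if it already does so.
3. **Reporting route.** Reconcile the same two passages with the charter's Safety Analyses, so that an email report is handled in the same way for SAE status and the relatedness question as a survey report.

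The cost is three response options, one change of input type, a few reworded sentences and an ethics amendment. No extra visits or staff are needed. The downside is a few more events to classify.
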